### Analysis of effectiveness

To evaluate whether the effect of the intervention varies according to the type of health problem(s), sociodemographic characteristics and home municipality will be used in linear mixed-effects models. Given the multilevel structure of the data (individuals over time within municipalities), we will control for stable differences between municipalities using a so-called fixed-effects model. Hence, we will control for time-invariant independent variables at the municipality level, such as the size of the municipality, demographics, and resources. In addition, the effect sizes will be calculated by dividing the difference of the mean change in the intervention groups and control groups by the standard deviation of the pretreatment scores.

### Analysis of cost-effectiveness

To assess the cost-effectiveness of reablement, we will need to estimate health outcomes and costs. The health outcomes will be measured using the EQ-5D and the costs will include health care sector costs. To estimate costs, we will include the cost of the intervention, which includes the hours, frequency, and type of training received in private homes according to health care professionals. Furthermore, the use of other health care services (home care services, rehabilitation, and institution) will be recorded for both the intervention and control groups over a period of 6 months. Standard methods for economic evaluation will be applied and the cost-effectiveness will be calculated as the incremental cost-effectiveness ratio, which is defined by the cost per incremental QALY. Further uncertainty will be determined by applying the bootstrap method with 1000 replicates to illustrate the variation in the patient population in terms of incremental health gains and costs.

### Ethics and dissemination

This study has been approved by the Regional Committee for Medical and Health Research Ethics for Western Norway (REK West, 2014/57). Participants will be coded and the analysis will be performed anonymously. The procedures will be conducted in accordance with the Declaration of Helsinki (1975), as revised in 2013 [34]. A declaration of voluntary participation with information about the study purposes and consequences, emphasizing the right to withdraw from the study, will be signed by each participant.

We will communicate the results in a report to the funder and in articles published in peer-reviewed journals. In addition, results will be presented to the municipalities involved in the study, health care professionals, and the public in general, through various national and international events and websites.

## Discussion

Reablement is a new and promising rehabilitation model, which is being implemented in several Western countries to meet current and future needs for home-based services [2]. However, there is limited evidence of the clinical and cost-effectiveness of this intervention.

The current trial will be a national multicenter study of reablement in Norway. To our knowledge, no previous study of reablement has included this many municipalities and participants in a nationwide clinical controlled trial. The multicenter design will ensure that the new program will be implemented in various settings, thereby enhancing the generalizability of the results.

This study has been registered with ClinicalTrials.gov (October 24, 2014) and it follows the SPIRIT 2013 statement [13], which defines standard protocol items for clinical items, thereby facilitating the transparency, proper conduct, reporting, and external review of the trial.

Patient-oriented outcome measures and procedures that help to enhance the role of the participant in the team care process as well as communication between health professionals were advocated in a review of the efficacy of multidisciplinary team care programs [35].

The primary outcome of this study will be the COPM, which is a patient-specific measure that allows each participant to choose and rate the activities that she/he considers important to perform in her/his daily life (cf. the manual [14]). The COPM captures the activities that are direct concerns for the individual, so the “noise” that is present in standardized instruments will be reduced, which theoretically has the potential to make this measure more responsive in capturing the effects of rehabilitation. In addition, the prioritized activities will be used as a basis for developing rehabilitation goals, thereby enhancing communication and giving an active role to the participants in the rehabilitation process.

Reablement is a complex intervention with a multicomponent nature; therefore, it is crucial to ensure congruence between the outcomes and the content of the intervention. Thus, several secondary outcomes are included, which have the potential to capture various effects in addition to the main outcome of COPM, such as improvement in coping and mental health. Furthermore, this study will also investigate the use of health care services and cost data, although some methodological limitations need to be discussed.

Compliance with the intervention and data collection procedures comprises a possible threat to the reliability of the study. This is a great challenge because a large number of municipalities are involved, as well as many different health care professionals. The reablement intervention is also individually tailored, which further increases the complexity. The intervention will vary between individuals, but also between municipalities, so it is important that all of the health care providers receive sufficient training and information. This will ensure that the correct way of implementing the intervention is understood and internalized, and that the data collection procedures are followed.

To ensure compliance with the study procedures, all municipalities will receive training. Furthermore, we will ensure that if a health professional leaves the study, then their replacement will receive sufficient training in both the intervention and the data collection procedures. In addition, the principal investigator will make regular contact with each municipality to ensure compliance with the procedures. The principal investigator will also check all of the incoming data material continuously to detect any misunderstandings and missing values, which will be corrected accordingly, if possible.

Another challenge is that the baseline COPM interview and scoring process might have a therapeutic effect, independent of the forthcoming interventions [36, 37]. The COPM interview may promote consciousness and motivation, and thus a process of change may also start in the control group, thereby diminishing the potential differences between the control and intervention groups.

In the present study, the allocation of participants to the intervention group or control group will not be randomized. As a consequence, its capacity to detect causal relationships will be weaker than that in a true experimental design. However, an important strength is that this study will occur in natural settings; hence, its practicality, feasibility and, to some extent, generalizability may be high. Furthermore, the controlled design will allow us to determine whether the participants in the two groups have similar baseline levels in terms of relevant clinical characteristics such as activity performance and coping [38]. If the groups are comparable at baseline, we may be relatively confident in inferring that any posttest differences are the result of reablement. In addition, if the results indicate initial differences, these may be controlled in the statistical analyses of between-group differences.

In summary, the findings of the present study may make an important contribution to our knowledge of rehabilitation approaches for community-dwelling adults. If the reablement model proves effective, it may also be applied within other fields of rehabilitation.

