#### Primary outcomes

The primary outcomes are activity performance and satisfaction with activity performance, which will be assessed by the COPM. The COPM measures a client’s self-perception of activity performance within nine activity areas; personal care, functional mobility, community management (self-care), paid/unpaid work, household management, play/school (productivity), and quiet recreation, active recreation, and socialization (leisure) [14]. The COPM starts with a semi-structured interview during which participants describe the activities that they consider to be important, but difficult to perform. Each activity is entered in one of the nine COPM activity categories and the importance of each activity is rated on a 10-point scale (10 = very important). The participant is then asked to choose up to five of the most important activities and to rate their performance and satisfaction with the performance of each activity on a scale from 1–10 (where a higher score reflects better performance and higher satisfaction). According to the COPM manual, a change of two points indicates a clinically relevant improvement or deterioration [14]. The Norwegian version of the COPM has been tested in terms of its psychometric properties with good results [15, 16].

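### Similar baseline COPM scores are an incomplete check on functional severity: add baseline SPPB and EQ-5D to the comparability statement and to every COPM model

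*Protocol article*

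**What the plan says.** The Discussion concedes that participants are not randomised and that causal inference is weaker for it. It then says that the controlled design will show whether the groups "have similar baseline levels in terms of relevant clinical characteristics such as activity performance and coping". Two consequences follow. First: "If the groups are comparable at baseline, we may be relatively confident in inferring that any posttest differences are the result of reablement". Second, "if the results indicate initial differences, these may be controlled in the statistical analyses of between-group differences".

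Under Primary outcomes the article identifies the instrument: "The primary outcomes are activity performance and satisfaction with activity performance, which will be assessed by the COPM". In the interview "participants describe the activities that they consider to be important, but difficult to perform", after which each person is asked to "choose up to five of the most important activities and to rate their performance and satisfaction with the performance of each activity". The Discussion describes the COPM as "a patient-specific measure that allows each participant to choose and rate the activities that she/he considers important". The content of the choice is recorded: "Each activity is entered in one of the nine COPM activity categories".

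Table 2 lists SPPB, EQ-5D, SOC-13 and MHC-SF at baseline, as well as main health challenge. Descriptive statistics says that baseline characteristics and all outcome measures will be described by group, with analysis of covariance for group differences at baseline and at the end of the intervention. Analysis of effectiveness names health problems, sociodemographic characteristics and municipality for the mixed models. It names no baseline measure of function.

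**The concern.** A baseline comparison supports a causal reading only as far as the compared variable means the same thing in both groups and tracks what could confound the outcome. The COPM has no common item set. A participant who cannot manage personal hygiene and one who cannot manage a long outdoor walk can give the same rating, because each rates a different, self-chosen, difficult task. Equal means then show equal self-rated difficulty on different tasks.

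Severity could plausibly differ between arms. Municipalities or zones define the arms, the zones were allocated on practical grounds by the municipality, and eligibility as described requires only a functional decline, with no threshold. If severity differs and also affects COPM at follow-up, a similar baseline COPM could be taken as reassurance that it does not give. Because adjustment is described as something that may follow if differences are seen, that reassurance could also mean that no function measure enters the model.

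**Working it through.** The article states no figure on this point, so there is none to reproduce. The reasoning rests on the text; the arithmetic shows only how the size depends on one unknown.

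**Chain in the text**
1. Allocation is not randomised (Sample size calculation; Discussion).
2. Baseline similarity on characteristics such as activity performance supports attribution to reablement (Discussion).
3. Activity performance is the COPM (Primary outcomes; Table 2).
4. COPM items are self-chosen and differ between people. Difficulty is the entry condition, and importance decides which activities are scored (Primary outcomes).
5. Hence similar COPM means do not by themselves show similar function.

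**Illustration of size**

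From the article: SD 2.5, target difference 1 point, minimum enrolment 107 control and 400 intervention, planned total about 750. Assumed: the arms differ by 0.5 SD in functional severity, and baseline COPM correlates r with severity.

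- Expected baseline COPM difference = 0.5 × r × 2.5 points.
- Standard error of a standardised difference at 107/400 = √(1/107 + 1/400) = 0.109. At 750 in the same ratio (about 158/592) it is √(1/158 + 1/592) = 0.090.
- Chance that a two-sided 5% baseline test flags the difference: normal power with standardised difference 0.5r.
- Share of the severity gap left after linear adjustment for baseline COPM = 1 − r².

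| Assumed r | COPM difference (points) | Flagged, 107/400 | Flagged, 158/592 | Severity gap left |
|---|---|---|---|---|
| 0.2 | 0.25 | 15% | 20% | 96% |
| 0.3 | 0.38 | 28% | 39% | 91% |
| 0.5 | 0.63 | 63% | 80% | 75% |
| 0.7 | 0.88 | 90% | 97% | 51% |

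**From severity gap to bias in the COPM effect**

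Assume also that severity has the same r with COPM at follow-up, and that COPM at baseline and follow-up correlate b = 0.3 to 0.7 with equal SDs. The bias left after adjusting for baseline COPM is 0.5 × r × 2.5 × (1 − b).

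- r = 0.2: 0.25 × 0.3 to 0.25 × 0.7 = 0.08 to 0.18 point.
- r = 0.3: 0.375 × 0.3 to 0.375 × 0.7 = 0.11 to 0.26 point.
- r = 0.5: 0.625 × 0.3 to 0.625 × 0.7 = 0.19 to 0.44 point.

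It would be larger if severity also predicted change in COPM by a separate route.

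**Simulation cross-check, all parameters assumed**

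There were 20,000 people per group, a true function gap of 1 SD, and five of 30 activities scored.

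- Activities chosen from those rated difficult: COPM means 4.49 and 3.60, within-group correlation with function 0.68, remaining function gap after COPM adjustment 0.51 SD (1 − 0.68² = 0.54).
- Activities chosen from all: correlation 0.79, remaining gap 0.38 SD (1 − 0.79² = 0.38).

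COPM carried real information about function in both runs, and adjustment for it left a substantial gap in both.

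**The case against.** The strongest reply is that the Discussion sentence is hedged and illustrative. COPM is one of two examples, no decision rule is set, and the same paragraph admits weaker causal capacity. Descriptive statistics already provides for baseline comparison by group, including SPPB and EQ-5D. Checking similarity on the primary outcome's own baseline is ordinary practice. Which covariates enter the COPM model is detail that an article may leave to the full protocol or analysis plan. All of this stands and limits the point.

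A reader might infer four stronger things, none of which the article supports:

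- That COPM is the sole or leading basis for judging comparability. The wording makes it an example.
- That baseline COPM is nearly unrelated to function, so that adjusting for it achieves almost nothing. The article gives no correlation. The 91% and 96% figures follow only from assumed r of 0.3 and 0.2, and the simulation gave about 0.7 to 0.8.
- That COPM should be dropped from the check. That would remove the primary outcome's own baseline, a legitimate covariate for precision and for starting level.
- That the primary result would be badly biased. If r is low, severity also confounds follow-up COPM only weakly: the bias above is 0.08 to 0.26 point for r of 0.2 to 0.3, against a 1-point target.

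What the reply does not remove is that the causal statement is made without the limit on COPM as a marker of severity, although the Discussion does mention another COPM limit, the possible therapeutic effect of the interview. Nor does the article give SPPB or EQ-5D a role in adjustment. The municipality fixed effects are aimed at stable municipality-level differences, not at a participant's own function at entry.

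**Conclusion.** The point holds in a limited form. Similar baseline COPM means are an incomplete check on functional severity, and adjustment for baseline COPM alone would leave part of any severity gap between arms. That follows from how the article defines the instrument and needs no numerical assumption beyond COPM being an imperfect proxy for function.

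The size cannot be fixed from the article. Over assumed r of 0.2 to 0.7, between 96% and 51% of the gap would remain. For an assumed 0.5 SD gap, bias in the COPM effect would be about 0.1 to 0.4 point over r of 0.2 to 0.5, under the further assumptions stated. Whether any severity gap exists is also unknown. This is an inexpensive improvement to the comparability statement and the model, not a defect that invalidates the primary analysis.

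**What to change.** 1. Keep baseline COPM in the comparability check and as a covariate. In the Discussion, rest the comparability statement also on the common baseline measures: SPPB, EQ-5D and main health challenge.
2. Enter baseline SPPB and EQ-5D with baseline COPM in every COPM effectiveness model, for performance and for satisfaction, whether or not a baseline difference is seen.
3. Tabulate by arm how the chosen activities fall across the nine COPM categories, so that a difference in what is being rated is visible.
4. Add a sentence to the Discussion stating that COPM items differ between people, so similar COPM means do not establish similar function.

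Everything needed is already collected at baseline. The cost is a few more covariates, one table and a short change of wording. Participants with a missing baseline SPPB or EQ-5D will need handling in the model.

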## Methods/design

### Design and setting

This will be a large multicenter clinical controlled trial. The study will be conducted in primary care settings in 44 of the 428 Norwegian municipalities, including eight municipalities that function as a control group; for three municipalities with two zones, one will be assigned to the control group and the other to the intervention group (see Fig. 1 for flow diagram). The allocation of zones to the intervention or control group was based on practical reasons and decided by the municipality. The municipalities included represent 17 % of the total population in Norway. The experimental group will be offered reablement and the control group standard treatment. The sample will comprise approximately 750 participants, who will be assessed at baseline and after 10 weeks, 6 months, and 12 months.

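### Allocation is not randomised, yet control for patient-level baseline differences is conditional and optional, and the effect size is an unadjusted difference in mean change

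*Protocol article*

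**What the plan says.** The Sample size calculation and the Discussion both state that allocation is not randomised; in the Discussion's words, "the allocation of participants to the intervention group or control group will not be randomized". Design and setting describes 44 municipalities, "including eight municipalities that function as a control group; for three municipalities with two zones" giving one zone to each arm. For those zones, "The allocation of zones to the intervention or control group was based on practical reasons and decided by the municipality".

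Four parts of the plan bear on baseline differences:

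- **Discussion.** "If the groups are comparable at baseline, we may be relatively confident in inferring that any posttest differences are the result of reablement". If the groups are not comparable, "if the results indicate initial differences, these may be controlled in the statistical analyses of between-group differences".
- **Statistical analysis and Analysis of effectiveness.** Municipalities are treated as fixed effects, and "we will control for stable differences between municipalities using a so-called fixed-effects model". This is stated without condition and is limited to time-invariant factors at municipality level. Patient characteristics appear for another purpose: "To evaluate whether the effect of the intervention varies according to the type of health problem(s), sociodemographic characteristics and home municipality will be used" in the mixed models.
- **Descriptive statistics.** A univariate analysis of covariance (ANCOVA) compares the groups at baseline and at the end of the intervention. No covariates are named.
- **Analysis of effectiveness, last sentence.** As an addition to the models, "the effect sizes will be calculated by dividing the difference of the mean change in the intervention groups and control groups" by the pretreatment standard deviation. No adjustment is mentioned.

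**The concern.** Without randomisation, adjustment for measured confounders is the main protection of the between-group comparison. Here it is left to an *if* and a *may*, and groups that look alike are taken to support a causal reading.

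That is unsafe for two reasons. A moderate imbalance can easily go unnoticed at these sample sizes, and similarity on measured variables says nothing about unmeasured ones.

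Patient-level selection is plausible. One arm offers intensive, goal-directed training. The other often consists of compensating help delivered according to what participants apply for. Table 2 records motivation for rehabilitation and health challenges at baseline, but the text does not commit to adjusting for either.

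At stake is whether a difference in case mix could be reported as an effect of reablement, most directly through the unadjusted effect size.

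**Working it through.** **Inputs from the Sample size calculation.** Difference to detect 1 COPM point; SD 2.5 (earlier study: 1.4 for performance, 1.6 for satisfaction); two-sided 5%; power 80%; intervention group three to four times the control group; 70/260 before and 107/400 after allowing for 35% dropout. The Abstract and Design and setting give about 750 participants.

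**Step 1: the plan's own figure.** With ratio k = 260/70 = 3.71:

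n(control) = (1 + 1/k) × (1.96 + 0.84)² × 2.5² / 1² ≈ 62.3, so 63 control and 234 intervention.

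The stated 70/260 is somewhat larger than its inputs require and has about 84% power. For dropout, 260/0.65 = 400 and 70/0.65 = 107.7 (stated as 107). The mismatch is in the safe direction and does not affect this point. The group sizes are used below as stated.

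**Step 2: how often would a 5% baseline test flag a true 0.5-point imbalance?** SE = SD × √(1/n₁ + 1/n₂); probability ≈ Φ(0.5/SE − 1.96). Clustering is ignored; it would lower these figures.

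| Groups | SD | SE | 0.5/SE | Flagged |
|---|---|---|---|---|
| 70/260 | 2.5 | 0.337 | 1.49 | 32% |
| 107/400 | 2.5 | 0.272 | 1.84 | 45% |
| 150/600 (750 at 4:1) | 2.5 | 0.228 | 2.19 | 59% |
| 187.5/562.5 (750 at 3:1) | 2.5 | 0.211 | 2.37 | 66% |
| 107/400 | 1.6 | 0.174 | 2.87 | 82% |
| 107/400 | 1.4 | 0.152 | 3.28 | 91% |

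**Step 3: what such an imbalance does to a raw change difference.** Assume equal variances and regression to a common mean, with baseline–follow-up correlation r (not given in the protocol). The shift is then (1 − r) × imbalance. For 0.5 points it is 0.15 (r = 0.7), 0.25 (r = 0.5) or 0.35 (r = 0.3), against a 1-point target. For a 1-point imbalance (0.4 SD) at r = 0.3 it is 0.70.

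**Step 4: do the fixed effects protect the comparison?** Outside the three split municipalities, each municipality has one arm. The 41 municipality indicators plus the arm indicator make 42 columns of rank 41, so the arm indicator is redundant there. A main effect of arm is identified only from the three split municipalities. An arm-by-time contrast stays estimable, but municipality effects do not protect it against patient-level confounders of change.

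**Step 5: illustration by simulation.** 4,000 runs, 70 against 260, SD 2.5, no true effect. The assumptions are one patient-level confounder, imbalanced by 0.2 to 0.5 SD, correlated 0.3 to 0.5 with change.

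| Rule | False-positive rate | Mean bias (points) |
|---|---|---|
| Never adjust | 7–45% | 0.15–0.62 |
| Adjust only if baseline p ≤ 0.05 | 4.3–6.0% | 0.00–0.12 |
| Always adjust | 4.2–5.3% | about 0 |

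**The case against.** The other side has a substantial case.

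- **Some adjustment is unconditional.** A reader might infer that all adjustment hangs on a baseline significance test. The documents do not support that: municipality fixed effects are planned outright, an ANCOVA is named, and no threshold is set as a trigger. The conditional wording comes from a limitations paragraph that concedes weaker causal capacity. This stands, but the fixed effects do not reach patient-level confounding, the ANCOVA names no covariates, and patient characteristics enter the models to study effect variation.
- **Municipalities choosing their own arm** might be inferred for the whole trial. It is stated only for the zones of the three split municipalities. For the others, the text says only that allocation was not randomised.
- **The detection figures depend on inputs.** With about 750 participants at SD 2.5, or 107/400 at the smaller SDs, a 0.5-point imbalance would be flagged more often than missed. This stands, which is why a range is given.
- **A change score is not simply wrong.** It subtracts the baseline level. If the groups' underlying means differ stably, the raw change difference is unbiased by that imbalance and baseline-adjusted ANCOVA can be biased. The shift in Step 3 needs regression to a common mean. This also stands, and the effect size is only supplementary.
- **Conditional adjustment did little harm in the simulation.** That is true where the one confounder is tested and is then adjusted for. The Discussion promises neither.

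A covariate list may sit in an analysis plan not shown here, so its absence is not the criticism. The criticism is the conditional wording and the unadjusted definition.

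**Conclusion.** The point holds in a limited form. Control of patient-level baseline differences is worded as conditional and optional, observed comparability is given more causal weight than it can bear, and the effect size is defined without adjustment.

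A 0.5-point baseline imbalance would be significant in about 32% to 66% of cases at SD 2.5, depending on the numbers analysed, and in 82–91% with 107/400 at SD 1.4–1.6. These figures ignore clustering. If undetected, it would move a raw change difference by 0.15 to 0.35 points for correlations of 0.7 to 0.3, but only under regression to a common mean.

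A reader might conclude that the primary comparison is unprotected or that its p-value is invalidated by pre-testing. The documents do not support that, given the planned fixed effects and the small harm from conditional adjustment in the simulation. This is a cheap and worthwhile improvement, not a change on which the trial's validity depends.

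**What to change.** 1. In the primary between-group model, adjust for baseline COPM and a prespecified set of patient-level covariates, whatever the baseline comparison shows. Candidates already collected at t1 in Table 2 are age, gender, living situation, education, motivation for rehabilitation, main and other health challenges, and baseline physical performance (SPPB) and EQ-5D.
2. State how municipality enters that model. If follow-up COPM is regressed on baseline COPM with municipality fixed effects, the arm effect rests on the three split municipalities alone (Step 4). If an arm-by-time contrast is used instead, the covariates need time interactions to adjust the change.
3. Describe baseline balance with standardised differences, and do not let it decide whether adjustment is made.
4. Base the effect size on the adjusted difference. Keep the raw change difference as a sensitivity analysis, because neither is uniformly unbiased without randomisation.
5. Reword the Discussion so that comparability on measured variables is not presented as enough for a causal conclusion, and acknowledge unmeasured confounding.

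Municipality size, which is not in Table 2, and a propensity-weighted analysis are not needed for this.

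The cost is a change of analysis wording, slightly more analysis work and some loss of cases with missing covariates. No new data are required.
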